This study protocol describes a randomized controlled trial of Pilates solo and belly dance (three times per week) for women after the diagnosis of breast cancer and compare its effects with a control group without intervention. The hypothesis is that the Pilates solo and belly dance protocol will promote improvement in primary (quality of life) and secondary (psychological and physical) outcomes in women after the diagnosis of breast cancer, providing a beneficial activity option for women with breast cancer. Our second hypothesis is that Pilates will lead to better improvements in the physical variables and belly dance will improve psychological variables.

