## Methods

### Study design

This is a single-center, prospective, three-arm randomized clinical trial designed to assess the effects of Pilates solo and belly dance among women undergoing clinical treatment of breast cancer on the primary outcome of quality of life and secondary outcomes of physical aspects, such as cardiorespiratory fitness, lymphedema, physical activity, disabilities of the arm, ROM, strength, and flexibility, and psychological aspects, such as depressive symptoms, body image, self-esteem, fatigue, pain, sexual function, and sleep quality. Participants will be randomized to either a Pilates solo intervention group, a belly dance intervention group, or the control group. This study is conducted according to the Standard Protocol Items: Recommendations for Interventional Trials (SPIRIT) 2013 checklist: recommended items to address in a clinical trial protocol and related documents (Additional file 1).

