### Sample size

To calculate the sample size, the method of distinguishing between the means was used, being n = (α + β) 2 σ2/d2. The values of α = 0.05 and β = 0.80 were adhered to, for which, according to the Gaussian curve table, values of 1.64 and 0.84, respectively, were used. The difference between the means was obtained through the pilot study, and a variable considered for the calculation was quality of life, in which an average of the difference between all the scales in the before and after periods was found. This value of the expected selection was 6.15 ± 9.4. The expected variance (σ2) was 89.49. At the end of the analysis, after inclusion of a 30% margin of sample loss, a sample of 19 patients was selected for each group. Figure 1 shows the flow diagram of the study participants.

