#### Statistical analysis

First, a spreadsheet will be created using the Excel 2016 software (Microsoft, Redmond, WA, USA), from which the data will be transferred to IBM SPSS Statistics version 20.0 software (IBM, Armonk, NY, USA) for analysis. Descriptive statistics (mean, standard deviation, and percentage) for the characteristics of the sample will be computed. To investigate the relationship between general and health information of the control and experimental groups, chi-square or Fisher’s exact tests will be used. To analyze differences in the experimental and control groups in the baseline, postintervention, and maintenance periods, two-way analysis of variance with repeated measures and Holm-Šídák comparison tests will be conducted. Confounder variables will be considered in the analyses as type of treatment, type of surgery, age, and weight status. The analysis will be performed according to the protocol and intention to treat, meaning that all the patients will be evaluated according to the randomization process. Missing data will be handled using the multiple imputation method. The significance level of 5% will be two-sided.

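### The 80% power in Sample size is for one test at 0.05 and does not describe the Holm-Šídák rule by which the three arms will be judged

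*Protocol article*

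**What the plan says.** The Study design section describes a "single-center, prospective, three-arm randomized clinical trial". The Sample size section gives the formula "n = (α + β) 2 σ2/d2" and states "The values of α = 0.05 and β = 0.80 were adhered to"; the 0.80 is labelled β but used as power. For these, "values of 1.64 and 0.84, respectively, were used". The effect comes from the pilot study's before-and-after change in quality of life: "This value of the expected selection was 6.15 ± 9.4", and "The expected variance (σ2) was 89.49". A 30% margin for loss brings the figure to 19 per group.

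The Statistical analysis section compares the groups at baseline, postintervention and the maintenance visits: "two-way analysis of variance with repeated measures and Holm-Šídák comparison tests will be conducted". The significance level there is 5%, two-sided. The article does not say which comparisons make up the Holm-Šídák family. The Background section names the comparison of each activity with control as the main question and adds "Our second hypothesis is that Pilates will lead to better improvements in the physical variables and belly dance will improve psychological variables".

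**The concern.** The alpha that sets the sample size and the alpha that decides whether an arm has worked are different. The sizing spends the full 0.05 on one comparison. Holm-Šídák shares 5% over several, and the smallest p-value must pass a stricter threshold. The 80% is the only statement of power in the article, and a reader will take it as the chance of showing that Pilates or belly dance beats control. If that chance is well under one half, a result that is not significant would be weak evidence of no benefit, and the published sizing would hide this.

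**Working it through.** **Inputs.** From Sample size: difference 6.15, variance 89.49 (SD 9.46), z values 1.64 and 0.84, loss margin 30%, 19 per group. From Statistical analysis: two-sided 5%, Holm-Šídák. From Study design: three arms.

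**1. The plan's own figure.** (1.64 + 0.84)² × 89.49 / 6.15² = 6.1504 × 89.49 / 37.8225 = 14.55. Then 14.55 × 1.3 = 18.9, so 19. The figure reproduces. It is a one-sided calculation for one mean, with no factor of 2 for two groups and no term for the number of comparisons. On those terms 15 women give 80.9% power. After 30% loss, 19 × 0.7 = 13.3, so about 13 per arm would be evaluable.

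**2. Thresholds under Holm-Šídák.** With three pairs the steps are 1 − 0.95^(1/3) = 0.0170, then 1 − 0.95^(1/2) = 0.0253, then 0.05. With only the two active-versus-control contrasts they are 0.0253, then 0.05. The article does not state the family, so both are carried forward.

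**3. Hand check at 19 per arm (normal approximation).** The standard error of a difference between two arms is √(2 × 89.49 / 19) = 3.07, and 6.15 / 3.07 = 2.00. Power is 51.7% for a two-sided test at 0.05, 40.8% at a fixed 0.0253 and 35.1% at a fixed 0.0170. At 13 per arm the three figures are 38.1%, 28.1% and 23.3%.

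**4. The actual step-down rule.** Simulation, 40,000 trials per scenario, pooled variance, both active arms 6.15 above control, one visit, no covariates. Power per active-versus-control contrast:

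| Evaluable per arm | One two-sided test at 0.05 | Holm-Šídák, two contrasts | Holm-Šídák, three pairs |
|---|---|---|---|
| 13 | 36% | 30% | 23% |
| 15 | 41% | 34% | 27% |
| 19 | 50% | 43% | 35% |
| 38 | 80% | 77% | 69% |

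The one-test column at 13, 15 and 19 is the noncentral t result. If only one active arm works, the two-contrast figures fall to 26%, 39% and 72% at 13, 19 and 38 per arm; the three-pair figures stay at 23%, 35% and 69%.

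**5. How the shortfall divides.** At 19 per arm, the one-sided, one-sample formula accounts for the drop from 80% to 50%. Holm-Šídák accounts for a further 7 points (50 − 43) to 15 points (50 − 35). Once the formula is corrected to two groups and two sides (38 per arm), Holm-Šídák still takes 3 points (80 − 77) to 11 points (80 − 69). Holding a contrast at a fixed 0.0170 with 80% power would need 50 evaluable per arm against 38.

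**The case against.** Four points can be made for the plan.

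First, Holm-Šídák is a standard and valid step-down method, and choosing it is no error. This stands. A reader might infer that it is stricter than three arms need and should give way to an overall three-arm test at 5% followed by pairwise tests at 5%. The documents do not support that. At one visit the gated rule gives about 42% per contrast at 19 per arm, against 35% for Holm-Šídák on three pairs but 43% on two contrasts, so any gain depends on a family that the article does not state. Nor is the exchange free. The gated rule holds 5% at one visit only, and the Primary outcome measure section makes quality of life primary at every time point. Run separately at four post-baseline visits, it has a simulated family-wise error of 17.5%, 16.4% and 13.4% for assumed between-visit correlations of 0.3, 0.5 and 0.7.

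Second, a reader might say that 15 points of power are wasted. That is the gap at 19 per arm between the three-pair rule and no multiplicity control at all. Only about 5 to 7 points separate the three-pair rule from the gated one. The threshold 0.017 is likewise an inference from a three-pair family; it is not a figure in the plan.

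Third, the one-sided, one-sample formula does more harm than the missing allowance for multiplicity. That is true, as step 5 shows, but correcting the formula alone would still leave a stated 80% that the decision rule does not deliver.

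Fourth, success might mean that at least one comparison is significant. The chance of that with both arms effective is about 48% (three pairs) to 54% (two contrasts) at 19 per arm, still far from 80%. At 38 per arm it would be 81% to 85%, so the definition of success matters to any restated figure.

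**Conclusion.** The point holds as a mismatch between two stated choices: the power is computed for one comparison at 0.05, and the arms are judged by Holm-Šídák at a two-sided 5%. Per active-versus-control contrast, the plan's own inputs give about 35% to 43% at 19 per arm and 23% to 30% at 13, with both arms effective.

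These figures rest on assumptions. The pilot's before-and-after change and its variance are taken as the between-arm difference and within-arm variance; the comparison is at one visit; and nothing is gained from covariates or repeated measures. Such gains would raise the figures. Including several visits in one Holm-Šídák family would lower them: with 15 comparisons the first step is 0.0034. Leaving the family to a statistical analysis plan is not itself a fault, but the power cannot be stated without it. The finding does not extend to the choice of Holm-Šídák.

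**What to change.** In Sample size, replace the statement of 80% at alpha 0.05 with the power per active-versus-control contrast under the two-sided Holm-Šídák rule of the Statistical analysis section. Name the family it covers (two contrasts with control or all three pairs, and one visit or several), and give the power at 19 per group and at the number expected after 30% loss. Say whether success means each contrast or at least one. Use a two-group, two-sided calculation, since the restated figure has no meaning otherwise.

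The analysis method does not change. The cost is a few lines of text and a short calculation, and the Trial status section says that the trial is still enrolling. The restated figure will be low, and the sponsor must then decide whether to enlarge the trial or to report it openly as having limited power.

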### Assessment

#### Primary outcome measure

The main aim of the study is to evaluate the impact of a 16-week Pilates solo and belly dance protocol on quality of life (≥ 2% of the baseline scores) in patients with breast cancer undergoing clinical treatment. Quality of life is the primary outcome at all time points of the study, namely baseline; postintervention; and 6, 12, and 24 months after intervention. Quality of life will be the primary outcome because it involves all the physical and psychological aspects of the life of women with breast cancer. Therefore, the maintenance collection will take place considering the modification in quality of life and other outcomes that the Pilates solo and belly dance intervention can promote in these women.

The primary outcome of quality of life will be investigated by using the European Organization for Research and Treatment of Cancer Quality of Life Questionnaire C30 (EORTC QLQ-C30) [39]. This instrument was created by the European Organization for Research and Treatment of Cancer (EORTC) in 1986, and this is the third version. Validated for the cancer population by Michels et al. [40], with Cronbach’s α values of 0.72 for global health, 0.86 for the functional scale, and 0.81 for the symptomatic scale.

The instrument consists of 30 questions, being multidimensional and self-applied. Its objective is to evaluate the quality of life in patients with cancer in the last 4 weeks. It presents five functional scales (physical, functional, emotional, social, and cognitive), a scale on global health status, three symptom scales (fatigue, pain, and nausea/vomiting), and six additional symptom items (dyspnea, appetite, constipation, diarrhea, and financial difficulties). The answers are presented in the form of a Likert scale following the classification 1 = not at all, 2 = a little, 3 = quite a bit, and 4 = very much. The only exception applies to the global health scale. This is composed of two questions that ask the patient to rate both health and quality of life in the last week according to grades of 1 to 7. In this case, 1 would be a poor quality of life and 7 a good quality of life.

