#### Data collection

Data will be collected using an interview format with a paper questionnaire and physical tests. The principal investigator of the study, who received previous training, will conduct a 50-min interview. The questionnaire will cover general and clinical information, quality of life, and psychological variables. The physical variables will be investigated by the specific tests. All data collection will be administered before the beginning of the intervention (baseline collection) and after the conclusion of the 16-week protocol (postintervention collection), as well as 6, 12, and 24 months after intervention (maintenance collection) (see Fig. 1). The maintenance collection will take place considering the health behavior change that the belly dance and Pilates solo intervention can promote in women with breast cancer.

For the control group, data collection will be conducted using the same paper-based questionnaire and tests applied to the intervention group, with data on general and clinical information, quality of life, and physical and psychological variables. The collection will be scheduled with the participants and will take place at the same intervals as for the experimental group, before the start of the intervention (baseline collection) and after conclusion (postintervention collection) by the same principal investigator, as well as 6, 12, and 24 months after the intervention (maintenance collection). All the data collection of intervention and control groups will occur at Santa Catarina State University.

Patients who discontinue in the intervention or control group who did not show for the meeting will be collected as well and analyzed as an intention-to-treat group. During the intervention and data collection, the researchers will collect spontaneous feedback from the patients to guarantee that the study will not have any adverse events. Data from all groups (experimental and control) will be held according to the principles of good clinical practice and the Declaration of Helsinki and will be treated with confidentiality, following the current privacy policy.

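### The planned repeated-measures ANOVA relies on sphericity across visits 4 to 28 months apart; change-from-baseline contrasts tested on its pooled residual would have wrong error rates, by an amount and in a direction the protocol does not fix.

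*Protocol article*

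**What the plan says.** The Statistical analysis section gives the purpose as "To analyze differences in the experimental and control groups in the baseline, postintervention, and maintenance periods". The method it names is "two-way analysis of variance with repeated measures", followed by Holm-Šídák comparisons and run in "IBM SPSS Statistics version 20.0 software". All periods therefore enter one model. The section lists confounders to be considered (type of treatment, type of surgery, age, weight status) and a two-sided 5% level. It does not mention sphericity, and it does not say which error term the comparison tests use.

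The Data collection section sets the visits. The first is before the intervention and the second is "after the conclusion of the 16-week protocol (postintervention collection"). The later ones are given by the words "as well as 6, 12, and 24 months after intervention (maintenance collection"). With 16 weeks taken as about 4 months, that is months 0, 4, 10, 16 and 28. Table 3 also lists a 3-month visit that the text does not.

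The section on the primary outcome opens with this statement of purpose: "The main aim of the study is to evaluate the impact of a 16-week Pilates solo and belly dance protocol on quality of life". It adds a threshold set relative to baseline scores. The next sentence reads: "Quality of life is the primary outcome at all time points of the study". The Sample size section takes its effect and SD from a before-after difference in the pilot study.

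**The concern.** A classical two-way repeated-measures ANOVA estimates one within-woman residual mean square and uses it for every within-woman contrast. That is valid only if the difference between any two visits has the same variance. Scores 4 months apart would ordinarily correlate more strongly than scores 28 months apart. A single residual then averages over short and long gaps: it overstates the noise in a 4-month change and understates it in a 28-month change.

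A sphericity correction would not cure this. It adjusts the degrees of freedom of the overall F test and leaves the standard error of each comparison unchanged.

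At stake would be power for change at the end of the programme, in a trial with 19 women per arm, and the false-positive rate of claims about maintenance at 24 months.

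**Working it through.** **Inputs from the protocol.** Three arms of 19; σ² = 89.49, so the SD of the before-after change is √89.49 = 9.46; effect 6.15; visits at about 0, 4, 10, 16 and 28 months; two-sided 5%. The plan's own figure reproduces: (1.64 + 0.84)² × 89.49 / 6.15² = 14.55, and 14.55 × 1.3 = 18.92, rounded up to 19.

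**Assumed, because the protocol does not give them.** Between-visit correlations, and equal variances at all visits unless stated.

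**Formulas.** With unit variance at each visit and r̄ the mean of the ten pairwise correlations:
- expected pooled residual: MSE = 1 − r̄
- variance of change used by the pooled test: 2(1 − r̄)
- true variance of change from baseline to visit j: 2(1 − r₀ⱼ)
- pooled SE / true SE = √[(1 − r̄)/(1 − r₀ⱼ)]

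**Worked example: 4-month correlation 0.7, exponential decay.** The correlation at a gap of g months is 0.7^(g/4). The ten pairs (gaps 4, 10, 16, 28, 6, 12, 24, 6, 18, 12) give 0.700, 0.410, 0.240, 0.082, 0.586, 0.343, 0.118, 0.586, 0.201 and 0.343. They sum to 3.609, so r̄ = 0.361 and MSE = 0.639.
- Postintervention: √(0.639 / 0.300) = 1.46, SE too large.
- 24 months after intervention: √(0.639 / 0.918) = 0.83, SE too small.

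**Simulated size** of a nominal 5% test of the difference in change between two arms, using the pooled residual, without multiplicity adjustment. "Floor" is the level towards which correlation decays.

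| Assumed correlation | SE ratio, post | SE ratio, 24 mo | Size, post | Size, 24 mo |
|---|---|---|---|---|
| 0.8 at 4 months, no floor | 1.57 | 0.79 | 0.3% | 12.1% |
| 0.7, no floor | 1.46 | 0.83 | 0.4% | 10.2% |
| 0.8, floor 0.3 | 1.47 | 0.83 | 0.5% | 10.4% |
| 0.7, floor 0.2 | 1.39 | 0.87 | 0.6% | 8.4% |
| 0.7, floor 0.4 | 1.28 | 0.91 | 1.2% | 7.2% |
| 0.6, floor 0.3 | 1.23 | 0.93 | 1.6% | 6.3% |
| slow decay, 0.6 toward 0.5 | 1.06 | 0.96 | 2.9% | 5.7% |
| equal, 0.6 | 1.00 | 1.00 | about 5% | about 5% |
| 0.4 for baseline-post, 0.6 elsewhere | 0.84 | 1.03 | 10.1% | 4.5% |

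The last row is the reversal: r̄ = (9 × 0.6 + 0.4)/10 = 0.58, and √(0.42/0.60) = 0.84. With a contrast-specific error term, size was 4.5% to 5.5% at every visit in every structure simulated. Adding Table 3's 3-month visit keeps the pattern (0.7, no floor: 1.39 and 0.80).

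**Power for a 6.15-point difference in 16-week change.** With its own error term, SE = 9.46 × √(2/19) = 3.07 and 6.15/3.07 = 2.00, so unadjusted power is about 50%. With the pooled residual it falls to 23% (0.7, floor 0.2), 30% (0.7, floor 0.4), 34% (0.6, floor 0.3) or 19% (0.8, floor 0.3).

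**Arm contrasts at a single visit.** The matching error is (between-women mean square + (k − 1) × MSE)/k, where k is the number of visits. Its expectation is the average visit variance. If visit variances are equal, this is correct whatever the correlations; simulated size was 4.6% to 5.3%.

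**The case against.** The strongest reply is that the protocol does not commit to the faulty test. Holm-Šídák adjusts p values and implies no error term; a repeated-measures analysis can use contrast-specific errors or multivariate tests, and naming the software does not settle which. The error term could also reasonably be left to a fuller analysis plan. This stands: the distortion is conditional on pooling. The named model is still one whose classical form needs sphericity, and nothing in the text qualifies it.

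Second, comparing groups in each period, baseline included, can be read as arm against arm at each visit, which is not distorted when visit variances are equal. This also stands. However, the plan's own effect is a before-after difference and its threshold is relative to baseline, so contrasts in change are a natural use of the model and are the exposed kind.

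Third, the correlations are assumed. Slow decay nearly removes the problem. Varied response to the programme could make baseline-to-post the lowest correlation, so that the postintervention test becomes anti-conservative. With 0.45 between baseline and every later visit and 0.6 elsewhere, both tests have a size of about 7%. So neither amount nor direction is known.

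A reader might infer that the test of the trial's main aim is certain to be too conservative at 16 weeks. The documents do not support that. Sixteen weeks is the length of the programme, and quality of life is declared primary at every time point; no 16-week change contrast is singled out.

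**Conclusion.** The concern holds in conditional form. The protocol fixes a model that relies on sphericity for visits where equal correlation at all gaps is unlikely. If arm differences in change from baseline are tested with the pooled residual, and correlation decays with time under roughly equal variances, actual size is about 0.4% to 3% at postintervention and about 6% to 10% at 24 months; the steepest decay tried gave 0.3% and 12.1%. With equal correlation there is no error. If baseline-to-post correlation is the lowest, the direction reverses (about 10% at postintervention). Single-visit arm contrasts keep their size when visit variances are equal.

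It would go too far to say that the plan as written necessarily makes the early test conservative and the late one liberal: that needs an error term and a correlation pattern the documents do not give. The point is worth acting on because a cheap alternative keeps about the nominal size in either case.

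**What to change.** Replace the ANOVA with a linear mixed model for repeated measures: arm, visit, arm-by-visit and the planned covariates; unstructured within-woman covariance; Satterthwaite or Kenward-Roger degrees of freedom; and a named simpler heterogeneous structure as fallback if the model does not converge. Apply the Holm-Šídák step to the visit-specific arm contrasts, each with its own standard error, and say whether each is a difference at the visit or a difference in change from baseline. If ANOVA is kept, state that each contrast uses its own error term and not the pooled residual.

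The cost is one or two sentences and slightly more analysis work, with no new data. The downside is estimating 5 × 6 / 2 = 15 covariance parameters from 3 × 19 = 57 women (6 × 7 / 2 = 21 if Table 3's 3-month visit is real), which is why the fallback should be named in advance.
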